#### Secondary outcomes

ARM: Parameter measures, including resting pressure, maximum contraction pressure, defecation threshold, and maximum tolerance capacity of the anal canal, will be recorded.EORTC QLQ-CR29 [23]: The EORTC QLQ-CR29 questionnaire is a commonly used tool for assessing the quality of life of CRC patients. It comprises 29 items categorized into six core dimensions (urinary problems, abdominal and pelvic pain, bowel problems, fecal incontinence, anxiety, and body image), four sex-related dimensions (male sexual activity, female sexual activity, impotence, and sexual intercourse difficulties), and seven standalone dimensions (bloating, dry mouth, hair loss, taste problems, skin problems, embarrassment about colostomy, and stoma care problems). Each question is rated on a specific scale, with a total score of 100. A higher score indicates more severe symptoms experienced by the patient, resulting in a greater impact on their quality of life.Pelvic floor EMG: The EMG assesses various parameters, including baseline wave amplitude, rapid contraction pressure, sustained contraction pressure variability, endurance contraction pressure variability, and post-baseline wave amplitude. These parameters are measured using the biofeedback treatment device to investigate the potential functional improvements in the puborectalis and anal sphincter muscles.

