### Methods in analysis to handle protocol non-adherence and any statistical methods to handle missing data {20c}

In cases where the lost-to-follow-up rates are below 20%, we will conduct an intention-to-treat analysis. Missing values will be replaced using single imputation procedures with the group mean.

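### The QLQ-CR29 is described as a total of 100 with one direction, but 3 to 4 of its 17 listed dimensions do not apply to a given stoma-free patient, so no one can complete such a total

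*Protocol article*

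**What the plan says.** Under Outcome {12}, Secondary outcomes, the protocol article divides the 29 items of the QLQ-CR29 into three blocks:

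- Six core dimensions, covering urinary and bowel function, continence, pain, anxiety and body image.
- A block on sexual function: "four sex-related dimensions (male sexual activity, female sexual activity, impotence, and sexual intercourse difficulties").
- The remaining block, which contains the stoma dimensions: "seven standalone dimensions (bloating, dry mouth, hair loss, taste problems, skin problems, embarrassment about colostomy, and stoma care problems").

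It then states one scoring rule and one direction for the whole questionnaire: "Each question is rated on a specific scale, with a total score of 100. A higher score indicates more severe symptoms".

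The inclusion criteria {10} admit adults of either sex with persistent defecation dysfunction after anus-preserving surgery, including patients whose temporary ileal stoma has been taken back. The exclusion criteria bar a permanent stoma only where it is unrelated to the cancer surgery.

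The secondary outcome analysis {20a} refers to QLQ-CR29 scores in the plural and applies the primary-outcome methods to them. For missing data, {20a} prescribes last observation carried forward (LOCF), and {20c} adds: "Missing values will be replaced using single imputation procedures with the group mean".

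**The concern.** A total with a fixed maximum presumes that every respondent can answer every component. Two features of the protocol's own list break that presumption in its own population. Some sex-related dimensions apply to one sex only. Two standalone dimensions, "embarrassment about colostomy, and stoma care problems", presuppose a stoma, whereas the eligible patients are described as passing stool through a preserved anus.

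Quality of life is one of the two effects named in Objectives {7}, and it appears again in the explanation of comparators {6b}. The QLQ-CR29 is the only instrument listed for it. If an analyst follows the sentence as a single total, the result rests on a sum that no participant can complete. Its components differ by sex, and its value depends on an unstated choice about the blanks. A single stated direction also leaves the reader unable to tell how dimensions such as sexual activity and body image are scored.

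**Working it through.** The article gives no QLQ-CR29 calculation to reproduce. The sample size concerns the primary efficacy rate and does not bear on this point. The check is a count of the listed dimensions against eligibility.

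**Inputs.** From Secondary outcomes: 6 core, 4 sex-related and 7 standalone dimensions, 2 of the 7 concerning a stoma. From the inclusion criteria: either sex, anus-preserving surgery, any temporary stoma reversed.

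**Step 1, dimensions listed.** 6 + 4 + 7 = 17.

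**Step 2, patient without a stoma.** 17 − 2 = 15.

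**Step 3, by sex.**

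- Woman: male sexual activity and impotence do not apply. 15 − 2 = 13.
- Man: female sexual activity does not apply. 15 − 1 = 14. If intercourse difficulties are asked of women only, 15 − 2 = 13.

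The article does not say who is asked about intercourse difficulties, so both values for men are shown. The assumption is that the dimension applies either to both sexes or to women only.

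**Step 4, share not applicable.** 17 − 14 = 3 and 17 − 13 = 4, that is 3/17 = 17.6% to 4/17 = 23.5%.

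**Step 5, what this does to a total out of 100.** As an illustration only, assume equal weights and count non-applicable dimensions as zero. The highest attainable total is then 100 × 13/17 = 76.5 for a woman and 76.5 or 100 × 14/17 = 82.4 for a man. The article states neither assumption. Even where both sexes have 13 dimensions, they are not the same 13.

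**Step 6, do the imputation rules repair it?** LOCF has no earlier value to carry forward for a question that never applied. A group mean has normally no observed value to average for the stoma dimensions. For a sex-specific dimension, it could only come from patients to whom the question applies. Neither rule mentions non-applicable items.

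**The case against.** The strongest reply is that no total is intended. The scoring sentence opens with each question being rated on a scale, the abstract and {20a} both speak of scores in the plural, and the Discussion stresses the instrument's several dimensions. No section says that dimensions are summed, gives weights, or names a composite endpoint. On this reading each scale runs to 100, and sex-specific scales are simply analysed in those who answered. The article is also condensed, and detailed scoring of a published questionnaire may sit in the full plan. This has force, and it limits the conclusion. It does not remove the point, because the article does state a total and one direction for the whole questionnaire, and nothing in it corrects that sentence.

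Four stronger readings are tempting but unsupported:

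- **Some dimensions run the opposite way, so the result could have the wrong sign.** Labels such as sexual activity and body image may suggest this, but the article gives no individual direction. It is a question for the authors.
- **Bowel benefit would be diluted by a calculable amount.** That needs invented effects and equal weights, which the article does not give.
- **The plan imputes women's answers from men's.** The rule in {20c} follows a sentence about loss to follow-up, and group there most naturally means the treatment arm. Neither rule says that a non-applicable question counts as missing. What stands is that no exception is made.
- **Quality of life cannot be validly derived.** Dimension scores among the patients to whom they apply can be computed from the same questionnaires.

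The exclusion criteria also do not bar every stoma, so the stoma limb is an inference from the inclusion criteria. The sex-specific limb does not depend on it: it alone leaves every patient without a complete set.

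**Conclusion.** The point holds as a defect in a stated scoring rule. Read as a single total, the QLQ-CR29 score in this article can be completed by no participant and would not be comparable between men and women. For a patient without a stoma, 3 to 4 of the 17 listed dimensions do not apply, and the stated imputation rules do not settle what to do with them. The count assumes that the patient has no stoma, as the inclusion criteria imply, and that intercourse difficulties apply either to both sexes or to women only.

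If a 0-100 score per scale was intended, the data and the analysis are unaffected by the total, but the sentence still needs correcting. The single direction should then be replaced by a direction for each scale. The outcome is secondary and the primary result does not depend on it. The correction is nevertheless worth making, because this is the only quality-of-life instrument listed for a stated objective.

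**What to change.** In Secondary outcomes, replace the total and the single direction with a separate 0-100 score for each dimension, in the direction given by the instrument's scoring manual. The authors should confirm the direction of dimensions such as sexual activity and body image. In the analysis section, state three rules:

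1. Sex-specific dimensions are analysed only within the sex to which they apply.
2. Stoma dimensions are not scored in patients without a stoma.
3. Non-applicable items are not missing data and are exempt from both the LOCF and the group-mean rule.

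Naming particular scales as the main quality-of-life outcomes is optional.

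The change is wording only: the questionnaire, the visits and the sample size stay as they are. The small cost is that there is no longer one headline quality-of-life number.

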### Participant timeline {13}

The participant timeline is outlined in the SPIRIT figure (Fig. 2).

**Fig. 2 Fig2:**
[figure not shown]
SPIRIT schedule of enrollment, intervention, and assessment

### Sample size {14}

Based on a prior study [10] involving 45 patients in each group (efficacy rate, 65.6%:46.7%), the required sample size for this study was computed utilizing the Power Analysis and Sample Size 15 software (NCSS Statistical Software, UT, USA). A sample size of 210 patients was determined to achieve a power (1-beta) of 0.80 and an alpha (significance level) of 0.05, with group allocation in a 1:1 ratio. Factoring in potential dropouts (15% of the participants), the total sample size was adjusted to 242 in total (*n* = 121 in each group).

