#### Secondary outcome analysis

ARM and EMG parameters, EORTC QLQ-CR29 scores: Analyzed using the same statistical methods as the primary outcomes.Statistical tests: continuous data: analyzed using Student’s *t*-tests, Mann-Whitney *U* tests, paired *t*-tests, and Wilcoxon signed-rank tests as appropriate. Categorical data: analyzed using chi-square tests or Fisher’s exact tests as appropriate.Reporting and significance: all *p*-values reported will be two-tailed. Confidence intervals will be set at the 95% level. Statistical significance will be defined as *p*-values < 0.05.

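### 242 is 210 × 1.15 and covers a 13.2% loss, not the stated 15%; and the 65.6% planning rate does not fit a whole count out of 45 patients and should be checked against its source

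*Protocol article*

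**What the plan says.** All the figures are in the protocol article, section Sample size {14}.

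- Source of the planning rates: "Based on a prior study [10] involving 45 patients in each group", with "efficacy rate, 65.6%:46.7" per cent.
- Base size: "A sample size of 210 patients was determined", for "a power (1-beta) of 0.80 and an alpha (significance level) of 0.05", "with group allocation in a 1:1 ratio". That is 105 per arm.
- Dropout step: "Factoring in potential dropouts (15% of the participants), the total sample size was adjusted to 242 in total", which is 121 per arm.

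The section does not say whether alpha is one- or two-sided. The Secondary outcome analysis section says that all p-values "reported will be two-tailed". The total of 242 is repeated in the Abstract and under Trial design, Recruitment and Sequence generation. The rates are efficacy rates, which corresponds to the responder definition under Primary outcome (improvement rate above 25%).

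**The concern.** Two figures in this short section do not agree with the figures next to them.

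The first is the dropout allowance. It is described as a share of the participants, so it must be taken from the number randomised. The arithmetic instead adds 15% to the number required, which always leaves too few patients.

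The second is the larger planning rate. It is presented as coming from groups of 45, but no whole number of patients out of 45 gives it. The difference between the two planning rates determines the base size of 210, so the reader needs to be able to trace it.

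At stake is whether 242 delivers the 210 evaluable patients that the plan sets itself, and whether the stated 80% power rests on a rate that can be verified.

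**Working it through.** **Inputs.** From Sample size {14}: p1 = 0.656, p2 = 0.467, alpha 0.05, power 0.80, 1:1 allocation, 210 before dropout, 15% dropout, 242 after dropout, 45 per group in the prior study. Two-sided testing is taken from the Secondary outcome analysis section.

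**Step 1: reproduce 210.** Two-proportion normal approximation with unpooled variance:

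n per arm = (1.960 + 0.842)² × [p1(1 − p1) + p2(1 − p2)] / (p1 − p2)²

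= 7.849 × (0.2257 + 0.2489) / 0.189² = 7.849 × 0.4746 / 0.03572 = 104.3, so 105 per arm and 210 in total.

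This is exactly the stated figure. The pooled-variance formula gives 108 per arm (216), which is close. One-sided versions give 166 to 190 and do not match.

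**Step 2: reproduce 242.** 210 × 1.15 = 241.5, rounded up to 242. This matches the plan.

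**Step 3: apply the stated loss.**

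- Remaining after 15% loss: 242 × 0.85 = 205.7, about 206 in total or 103 per arm.
- Total needed to keep 210: 210 / (1 − 0.15) = 247.06, so 248 with equal arms (124 each), 6 more than 242.
- Loss that 242 does cover: 1 − 210/242 = 13.2%.

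**Step 4: power at the stated rates.** On the unpooled formula, power = Φ(0.189 / √(0.4746/n) − 1.960).

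- n = 105: Φ(2.811 − 1.960) = 80.3%.
- n = 103: Φ(2.784 − 1.960) = 79.5%.

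The slip costs about 0.8 points. On the pooled formula the figures are 79.2% and 78.5%, a cost of about 0.7 points.

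**Step 5: check the rates against 45 patients.**

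- 21/45 = 46.7%, which fits.
- 0.656 × 45 = 29.52, not a whole number. The neighbours are 29/45 = 64.4% and 30/45 = 66.7%.

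**Step 6: what the neighbouring rates would imply,** each against 21/45 (unpooled, with pooled in brackets):

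| Larger rate | Power, 105 per arm | Power, 103 per arm | Power, all 121 per arm |
|---|---|---|---|
| 64.4% | 75.0% (74.0%) | 74.2% (73.2%) | 80.7% (79.9%) |
| 65.6% v 46.7%, as printed | 80.3% (79.2%) | 79.5% (78.5%) | 85.5% (84.6%) |
| 66.7% | 84.8% (83.8%) | 84.1% (83.0%) | 89.4% (88.6%) |

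At 64.4%, 80% power needs about 119 evaluable per arm (122 pooled). At 66.7% it needs fewer than the plan provides (pooled: 192 in total).

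**The case against.** The strongest reply is that the calculation is basically sound. The base figure of 210 reproduces exactly from the stated inputs. Six patients, about 2.5% of 242, is small against a dropout rate that is itself a guess, and the power lost is under one point. That stands, and it limits the weight of this point. It does not make the sentence correct: 15% of the participants is a definite statement, and 242 does not satisfy it.

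On the planning rate, a reader might infer that the plan misquotes its source, or that the trial does not have 80% power. The documents support neither. The prior study is not available. Its efficacy rate may rest on another denominator (21/32 is also 65.6%) or on a model estimate. The direction is open too: one neighbouring value lowers the power and the other raises it. The stated power is also conditional on the assumed rates, and at those rates 210 gives 80%. With 45 per group, the standard error of the difference is √(0.4746/45), about 10 points, so a shift of 1.1 points is small beside the uncertainty in the planning estimate. What remains is that rate and denominator, as printed, do not fit as a simple proportion.

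Group-mean imputation, planned in the section on non-adherence and missing data, would formally keep all 242 in the analysis. It adds no information about the lost patients, so it does not make up the shortfall.

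Finally, the power figures belong to the comparison of responder proportions used for the sample size. The Primary outcome analysis section lists t-tests and rank tests on LARS scores and improvement rates. The percentages here do not measure the power of those tests.

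**Conclusion.** The dropout step is wrong as written. 242 covers 13.2% loss; 15% loss leaves about 206 evaluable patients, 4 to 5 short of the plan's 210, and 248 would be needed to cover it. The consequence is small: power of 79.5% instead of 80.3% for the responder comparison, assuming the stated rates, a two-sided 0.05 test, the unpooled formula that reproduces 210, and losses shared equally between arms.

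The 65.6% rate is an unexplained discrepancy, not a demonstrated error. It does not correspond to a whole count out of 45, while 46.7% does. If the source figure turned out to be a neighbouring value, power at about 103 per arm would be about 73–74% (64.4%) or 83–84% (66.7%). Which applies, if either, cannot be told from the article. The stated power therefore cannot be fully traced, but it is not shown to fail.

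**What to change.** 1. Correct the dropout sentence in Sample size {14}. Either state that 242 randomised allows for about 13% loss while keeping 210 evaluable, or state that 242 with 15% loss leaves about 206 evaluable with about 79% power. It can be added that 248 is the total that would cover 15%.
2. Check 65.6% against the count and denominator in the prior study and cite both. If the rate comes from a different denominator or a model, say so. If it changes, restate the power.
3. Name the formula and the two-sided alpha next to the calculation, and say that the power refers to the comparison of responder proportions (improvement above 25%).

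The cost is wording only. No extra enrolment is needed to make the statement true. The one drawback of the dropout correction is a slightly less favourable stated figure, for either the loss allowance or the power. Whether item 2 moves the stated power up, down or not at all depends on the source.

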### Recruitment {15}

We aim to recruit 242 patients diagnosed with LARS, who meet eligibility criteria, from the inpatient and outpatient departments of the two hospitals. Our recruitment strategy includes targeted posters displayed in both hospital facilities and dissemination of health education brochures to potential participants. We will leverage mobile applications to disseminate recruitment information efficiently.

## Assignment of interventions: allocation

### Sequence generation {16a}

Using SAS software (9.3), the Clinical Evaluation and Analysis Centre at SRRH will randomly allocate 242 participants in a 1:1 ratio to the intervention group (undergoing B-PEPNS) or the control group (undergoing biofeedback alone). Professionals overseeing allocation will not be directly involved in the study.

### Concealment mechanism {16b}

Sequentially numbered opaque envelopes will conceal the random allocation, keeping it confidential from other research staff.

### Implementation {16c}

During the post-baseline assessment, an impartial staff member will open the envelope in the participants’ presence, assigning them to the intervention or control group. Simultaneously, the operators will receive information about the participant’s allocation. The recruitment staff and clinical interviewers will remain unaware of the group allotments to uphold study integrity.

## Assignment of interventions: blinding

### Who will be blinded {17a}

Throughout the trial process, data collectors, statisticians, and telephone follow-up personnel will be blinded. However, the operators will be aware of the group allocations but will not be involved in data recording, statistical analysis, or follow-up procedures. They will operate independently without any communication.

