### Criteria for discontinuing or modifying allocated interventions {11b}

If a needlestick infection occurs during PEPNS, the treatment will be delayed, and antibiotics will be administered. If symptoms improve within 1 week, treatment will continue. If symptoms do not improve within 1 week, or if another infection occurs after improvement, treatment will be terminated. Meanwhile, this should be reported as an adverse event. And if any other unforeseen serious side effects occur, the intervention will also be terminated.

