### Outcome {12}

Before commencing the treatment regimen, comprehensive patient information will be compiled, including demographic data, tumor metrics, surgical specifics, and any prior radiotherapy or chemotherapy received. Patients will undergo evaluations using the LARS and European Organization for Research and Treatment of Cancer Quality of Life Questionnaire-Colorectal 29 (EORTC QLQ-CR29) scoring systems along with anorectal manometry (ARM) and pelvic floor EMG assessments. These evaluations will be conducted at the following three key times: baseline, post-intervention (at 1 month), and during follow-up (at 6 months).

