### Adverse event reporting and harms {22}

The study will monitor for PEPNS-related adverse events (AEs), such as needle-related infections, and report them to the Ethics Committee. We will document the site, extent, treatment process, and recovery time of each AE, and assess the causality between AEs and the intervention. AEs will be used as safety outcome measures to evaluate the safety of the intervention.

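### The blinding section bars operators from recording or communicating with no safety exception, and the safety committee seats outcome assessors to whom a needle-site event would reveal the arm

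*Protocol article*

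**What the plan says.** Section {17a} of the protocol article names the masked roles: "data collectors, statisticians, and telephone follow-up personnel will be blinded". It then sets the rule for those who deliver treatment. The operators know the allocation but "will not be involved in data recording, statistical analysis, or follow-up procedures. They will operate independently without any communication". It does not say with whom communication is barred, and it has no exception for safety.

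Two other sections set duties for harms. Section {22} states: "The study will monitor for PEPNS-related adverse events (AEs), such as needle-related infections, and report them to the Ethics Committee". It continues: "We will document the site, extent, treatment process, and recovery time of each AE, and assess the causality between AEs and the intervention". Section {11b} makes the continuation of treatment after a needle infection depend on its course over one week, and says of the infection: "Meanwhile, this should be reported as an adverse event". Neither section says who records the event or how it reaches the safety record.

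Three further sections bear on the point. Section {18a} provides two days of training for therapists, acupuncturists and assessors, and includes data collection in its content. Section {21a} sets up an internal safety committee made up of the primary-outcome assessors and the principal investigator. Section {17b} opens the allocation after a serious adverse event and is silent on non-serious ones.

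**The concern.** The acupuncturists are the staff whom the article places at the needle sites, so they are best placed to see a local harm and follow its course. The blinding section, as worded, keeps them from recording it or passing it on. A site that takes the wording at face value has no clear way to meet {11b} and {22} through the people who first see the event.

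The second half of the problem lies at the receiving end. If a needle-site event is recorded and reaches the committee described in {21a}, it is read by people who also assess the primary outcome. Control patients have no needles, so the record tells the reader which arm the patient is in.

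Two things are at stake. Adverse events are the declared safety measure in {22}, and the introduction promises a comparison of safety as well as efficacy. The Discussion also accepts that participants and therapists cannot be blinded, and relies on independent data collection and processing to limit the resulting bias. Masked assessment is therefore one of the main protections left.

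**Working it through.** No figure in the article can be recomputed for this point. The check sets the sections side by side.

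1. **Who is at the needle sites.** Under {11a}, acupuncturists place needles at four points, Monday to Friday for 4 weeks: 5 × 4 = 20 sessions, which agrees with the 20 in the abstract. With 121 patients planned in the B-PEPNS arm, that is 121 × 20 = 2,420 scheduled sessions and 2,420 × 4 = 9,680 needle placements. These are occasions on which a harm could be seen, not events. The control arm has biofeedback only.

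2. **What operators may do.** Under {17a}: no data recording, no follow-up procedures, no communication.

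3. **What other sections need.**
   - {11b}: an infection is reported, and its course over a week is known. Someone who sees the site must pass on information.
   - {22}: site, extent, treatment, recovery time and causality for each event. This is data recording on any ordinary reading.
   - {18a}: acupuncturists are trained in data collection, which {17a} then appears to forbid them.

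   Taken literally, {17a} is at odds with all three.

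4. **Where the record goes.** Section {21a} sends safety data to a committee that includes the primary-outcome assessors. Section {17a} masks data collectors. The article does not state that these are the same people, but someone who assesses the primary outcome would ordinarily be counted among them.

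5. **Whether the record reveals the arm.** The events monitored under {22} are PEPNS-related, and only one arm receives PEPNS. Such a record identifies the arm without any formal unblinding. Section {17b} deals with serious events only, so a non-serious needle infection, which is the article's own type of example, falls under no rule.

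6. **Size.** The documents give no event rate. If the risk of a needle infection per patient were 1%, 5% or 10% (assumed values), the expected number of B-PEPNS patients with such an event would be 121 × 0.01 = 1.2, 121 × 0.05 = 6.1 or 121 × 0.10 = 12.1. These are patients for whom an arm-revealing record could arise. They are not a count of lost records or unmasked assessments.

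7. **Which outcomes are exposed.** LARS and QLQ-CR29 are answered by participants who already know their treatment, so unmasking an assessor adds little there. Manometry and pelvic floor EMG are run by an examiner, and masking that examiner has more to protect.

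**The case against.** The strongest reply is that {17a} should be read in context. It is the blinding item. It first lists masked collectors, statisticians and telephone staff, and then keeps operators out of the matching tasks. On that reading, data recording means outcome data and the bar on communication means contact with masked staff. Section {11b} expects treatment to be delayed, resumed or ended, which could not work if operators spoke to nobody. This is a plausible account of the intention. The text does not say it, however, and sites work from the text.

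A reader might go further and infer that operators are the only staff who see needle-site harms, so that each event must either go unrecorded or unmask a collector. The documents do not support that. Inspectors monitor treatments at each center ({18a}), an unspecified member of the team discusses the treatment experience with patients weekly ({11c}), the principal investigator sits on the safety committee ({21a}), and unmasked participants can report harms themselves. Any of these could supply a record. Sections {11b} and {22} also require recording, so it cannot be said that events will be lost. What remains is that none of these people is given the task, and that the principal investigator shares the committee with the outcome assessors.

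A third reply is that a condensed article may leave the adverse event form and its routing to the full protocol. That is fair for the form itself. It is also why little weight can rest on the outcome section, which lists the efficacy measures and says "These evaluations will be conducted at the following three key times: baseline, post-intervention (at 1 month), and during follow-up (at 6 months" without mentioning an adverse event enquiry: harms have their own section, and the schedule figure is not reproduced in the text available. But the point here is a conflict between rules that the article does state, and the committee's composition is stated too.

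**Conclusion.** The point holds as a conflict of wording with a real route to unmasking. Read literally, {17a} is incompatible with {11b}, {22} and the training in {18a}, and {21a} gives arm-revealing safety data to staff whom {17a} appears to mask. The second part assumes that the primary-outcome assessors are among the masked data collectors; the article implies this without stating it.

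The size is unknown, because it depends on an event rate that the documents do not give and on how sites read {17a}. The effect on LARS and QLQ-CR29 is limited by the participants' own knowledge of their treatment. The consequence lies mainly in the completeness of the harms record and in the masking of examiner-run manometry and EMG. That, with the very low cost of correction, makes it worth changing. It does not show that harms will be missed or that the primary comparison is invalid.

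**What to change.** Reconcile {11b}, {17a}, {17b}, {21a} and {22}, leaving the clinical rule in {11b} as it is:

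- **{17a}:** limit the ban to outcome data and to communication with masked staff, and state that safety reporting is exempt.
- **{22}:** have operators record adverse events at treatment sessions in both arms on a separate safety form, sent to named existing staff who take no part in outcome collection. Recording in both arms allows the promised safety comparison.
- **Access:** keep the form from data collectors, telephone staff, primary-outcome assessors and the statistician until the efficacy data are locked.
- **{21a}:** amend the committee's composition or its access so that outcome assessors do not review arm-revealing safety data.
- **{17b}:** say how non-serious events that reveal the arm are handled.
- **1- and 6-month visits:** ask about adverse events only after LARS, QLQ-CR29, manometry and EMG have been recorded.

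The independent Clinical Trials Office members named in {5d} might receive the forms, provided they are confirmed to be outside outcome collection. The article describes them only as part of a group that meets monthly on progress and on financial or technical issues, so the treatment decision in {11b} should not be moved to them.

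The cost is protocol wording, one extra form and a few minutes of operator time. Sample size, treatment and outcome measures are unaffected.
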